**Patient reported outcomes**	
Patient global score, pain, and fatigue	The patient’s general assessment of the influence of disease on global health, pain, and fatigue is indicated on a VAS [45, 46].
BASDAI	The patient indicates the severity of six types of discomfort related to disease activity on six individual VAS, including the degree of back pain. A BASDAI index is hereafter calculated based on the patient’s replies to the questions [47].
BASFI	The patient indicates the ability to perform ten actions or movements on a VAS. The questions are primarily related to axial arthritis. A BASFI index is hereafter calculated based on the patient’s replies to the questions [48].
HAQ	The patient’s functional status is assessed using a questionnaire with 20 questions that evaluates how difficult it is for the patient to perform normal daily activities divided into eight different categories. The questions are primarily related to peripheral joints. The degree of overall pain on a VAS is included. A HAQ score is calculated. The questionnaire is extended to include five additional questions (two categories) in relation to axSpA [49].
EQ-5D	The patient’s assessment of the health-related quality of life (HRQoL) with EQ5D comprises five questions about five different domains of HRQoL and a VAS on the patient’s perception of his/her/their health [50].
ASAS Health Index	ASAS Health Index is a questionnaire that measures functioning and health across 17 aspects of health and nine environmental factors in patients with SpA [51].
PASS	PASS is defined as the highest level of symptom beyond which patients consider themselves well. A question about disease status as assessed by the patient at the current visit with the last visit as an anchor, and whether the patient finds the current state of disease activity acceptable (yes/no) [52].
PsAID-9	The PsAID Questionnaire is a patient-reported outcome measure of disease impact in PsA and its domains are entirely patient-generated [53].
WPI	The WPI quantifies the extent of bodily pain on a 0–19 scale by asking patients if they have had pain or tenderness in 19 different body regions (shoulder girdle, hip, jaw, upper arm, upper leg, lower arm, and lower leg on each side of the body, as well as upper back, lower back, chest, neck, and abdomen) over the past week, with each painful or tender region scoring 1 point [54].
Injection Site Questionnaire	A questionnaire that was developed for this study uncovering the overall injection experience with Taltz. Patients mark the box that best fits their injection experience (very satisfied, somewhat satisfied, neither satisfied nor dissatisfied, somewhat dissatisfied, very dissatisfied)

*ASAS* assessment in SpondyloArthritis International Society, *ASDAS* Ankylosing Spondylitis Disease Activity Score, *CRP* C-reactive protein, *VAS* Visual analog scale*, BASMI* The Bath Ankylosing Spondylitis Metrology Index, *DAS* Disease Activity Index, *DAPSA* Disease Activity Index for Psoriatic Arthritis, *CDAI* Clinical Disease Activity Index, *MCP* Metacarpophalangeal, *PIP* Proximal interphalangeal, *DIP* Distal interphalangeal, *MTP* Metatarsophalangeal, *SPARCC* The Spondyloarthritis Research Consortium of Canada, *SpA* Spondyloarthritis, *ACR* American College of Rheumatology, *BSA* Body Surface Area, *BASDAI* The Bath Ankylosing Spondylitis Disease Activity Index, *BASFI* The Bath Ankylosing Spondylitis Functional Index, *HAQ* Health Assessment Questionnaire, *PASS* Patient Acceptable Symptom State, *PsAID* Psoriatic Arthritis Impact of Disease, *WPI* Widespread Pain Index

**Table 2 Tab2:** Summary of measures to be collected

Visit number	S	1	2	3	4	5	6	7	8
**Month***	− 1/2	0	2	4	6	9	12	18	24
**Inclusion related procedures**									
Informed consent	X								
Clinical history	X								
Past medical & surgical history	X								
Inclusion & exclusion criteria	X	X							
**Background factors**									
Gender & age	X								
Diagnosis (axSpA, PsA)	X								
Symptom duration & year of diagnosis	X								
Tobacco	X								
Height (cm) & weight (kg)	X								
**Patient-reported outcomes**									
Patient global score, pain & fatigue	X	X	X	X	X	X	X	X	X
BASDAI, BASFI, HAQ, EQ-5D, ASAS Health Index	X	X	X	X	X	X	X	X	X
PASS, PsAID-9, WPI	X	X	X	X	X	X	X	X	X
Injection site questionnaire			X						
**Clinical evaluation & composite indices**									
ASDAS CRP	X	X		X			X		X
Inflammatory back pain	X	X		X			X		X
BASMI	X	X		X			X		X
DAS28 CRP, CDAI, DAPSA, MDA	X	X		X			X		X
Swollen and tender joint count	X	X		X			X		X
Enthesitis (SPARCC and Leeds)	X	X		X			X		X
Tender points	X	X		X			X		X
Physician global (VAS 0-100 mm)	X	X		X			X		X
Extraarticular SpA features **	X	X		X			X		X
Physical examination*** incl. blood pressure & pulse	X	X		(X)			(X)		(X)
**Evaluation of treatment effect**									
ASDAS Low disease activity (axSpA)				X			X		X
DAPSA Low disease activity (PsA)				X			X		X
**Imaging**									
WB-MRI (incl. Synthetic CT)	X			X			X		X
Low-dose CT of SIJs & spine	X						X		X
Radiography of SIJs & spine	X								X
Radiography of thorax	X								
**Laboratory procedures**									
HLA-B27, anti-CCP & RF	X								
hCG (serum or urine, women only)	X	(X)	(X)	(X)	(X)	(X)	(X)	(X)	(X)
Screening blood tests**** before “biologics” incl. ANA	X								
Routine blood tests***** incl. CRP	X	X	X	X	X	X	X	X	X
Blood samples stored for biobank		X		X			X		X

X = assessed, (X) = assessment optional. *axSpA* axial spondyloarthritis, *PsA* Psoriatic Arthritis, *BASDAI* The Bath Ankylosing Spondylitis Disease Activity Index, *BASFI* The Bath Ankylosing Spondylitis Functional Index, *HAQ* Health Assessment Questionnaire, *ASAS* assessment in SpondyloArthritis International Society, *PASS* Patient Acceptable Symptom State, *PsAID* Psoriatic Arthritis Impact of Disease, *WPI* Widespread Pain Index, *ASDAS* Ankylosing Spondylitis Disease Activity Score, *CRP* C-reactive protein, *BASMI* The Bath Ankylosing Spondylitis Metrology Index, *DAS* Disease Activity Index, *CDAI* Clinical Disease Activity Index, *DAPSA* Disease Activity Index for Psoriatic Arthritis, *MDA* Minimal Disease Activity, *VAS* Visual analog scale, *SpA* Spondyloarthritis, *WB-MRI* Whole-body magnetic resonance imaging, *CT* computed tomography, *HLA-B27*, human leukocyte antigen B27, *anti-CCP* anti-citrullinated protein, *RF* rheumatoid factor

*A month is defined as 30 days

**Extraarticular SpA features include presence of symptoms/signs of activity in the following: anterior uveitis or scleritis, inflammatory bowel disease, dactylitis, skin or nail psoriasis, and heel enthesitis

***Examination of the general condition, oral cavity, lymph nodes (e.g., head, neck, axils, and groin), heart and lungs, abdomen, joints, entheses, and skin. A neurological examination should be performed if relevant based on the history of previous diseases

**** Screening blood tests: Tuberculosis (QuantiFERON®-TB Gold In-Tube test or T-SPOT®.*TB* test), hepatitis B virus (HBsAg and anti-HBs), hepatitis C virus (anti-HCV), anti-nuclear-antibodies (ANA)

*****Hemoglobin, leukocytes including differentials, platelets, albumin, alanine transaminase, alkaline/basic phosphatase, and creatinine

### Registration of adverse events and adverse reactions

A risk assessment of the trial in regard to risk-adjusted management of adverse events (AE) and adverse reactions (AR) based on the Danish Medicines Agency guidelines was performed. Based on the following, the trial was assessed as a “low-risk” trial (risk level 1): 1) The Investigational Medicinal Product (IMP) is post-marketing and is not subject to stricter reporting requirements as per DKMA list available at the webpage (https://laegemiddelstyrelsen.dk/en/sideeffects/side-effects-of-medicines/medicines-with-stricter-reporting-requirements/), 2) the intervention is similar to standard clinical treatment, and 3) the intervention and the IMPs base of evidence concerning safety is robust^1^

Implementation of a risk-adjusted management of AE and AR is therefore justified.

As the trial is assessed as a “low-risk” trial, level 1 (see above), only suspected unexpected serious adverse reactions (SUSARs) are recorded and reported. Because only SUSARs are registered, it is the responsibility of the investigator to assess causality in case of AEs.

### Endpoints

#### Primary endpoint

The primary endpoint is the change from baseline to month 12 in the total inflammatory burden in the entire body (peripheral and axial joints and entheses), as assessed by WB-MRI, in patients with axSpA and PsA treated with ixekizumab.

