In this study, we aim to address the abovementioned gaps by conducting a longitudinal investigation of the effects of ixekizumab on peripheral and axial inflammation and structural damage in patients with axSpA and PsA. Through comprehensive assessment using advanced imaging techniques such as WB-MRI and detailed MRI evaluation of the spine, including sCT, and low-dose CT, we seek to provide valuable information on the therapeutic effectiveness of ixekizumab across different disease domains. The primary objective is to assess the effect of ixekizumab on the total inflammatory burden in the entire body (peripheral and axial joints and entheses) of patients with axSpA and PsA, as assessed by WB-MRI.

Here we report the design of the DAPHNE study.

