### Assessments

During the 2-year study period, patients will have eight visits to the outpatient clinic, three of which are major assessment visits (months 4, 12, and 24) (see Fig. 1, dark blue arrows). At the major assessment visits, treatment efficacy, and disease activity are evaluated. Patients with ASDAS low disease activity (ASDAS ≤2.1) (axSpA) or DAPSA low disease activity (DAPSA ≤14) (PsA) continue treatment with sc. inj. ixekizumab 80 mg every 4 weeks. Patients, who are not responding (defined as having ASDAS > 2.1 or DAPSA > 14), change treatment at the discretion of the treating rheumatologist and according to the available guidelines from the Medicine Council, Danish Regions (Medicinrådet, Danske Regioner), and they continue to be followed in the study.

All protocol-related assessments will be entered into an electronic case report dedicated to the DAPHNE study.

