**Key secondary endpoints**	
1.	Change from baseline to *months 12 and 24* in *peripheral enthesitis*, as assessed by WB-MRI, in patients with axSpA and PsA treated with ixekizumab.
2.	Change from baseline to *months 12 and 24* in *peripheral joint inflammation*, as assessed by WB-MRI, in patients with axSpA and PsA treated with ixekizumab.
3.	Change from baseline to *month 24* in *total inflammatory burden in the entire body* (peripheral and axial joints and entheses), as assessed by WB-MRI, in patients with axSpA and PsA treated with ixekizumab.
4.	Description of *patterns of structural damage in sacroiliac joints and spine* in patients with axSpA and PsA by conventional MRI methods, MRI-based synthetic CT, low-dose CT, and radiography.
5.	Description of *changes in structural damage in sacroiliac joints and spine* in patients with axSpA and PsA by conventional MRI methods, MRI-based synthetic CT, low-dose CT, and radiography, during 2 years of therapy with ixekizumab.

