**Other secondary endpoints**	
1.	Change from baseline to *months 4, 12, and 24* in *axial inflammation*, as assessed by MRI, in patients with axSpA and PsA treated with ixekizumab, including separately in the posterolateral elements of the spine (facet joints, costovertebral joints, transverse processes, spinous processes, and perientheseal soft tissues) and in the vertebral bodies.
2.	Change from baseline to *months 4 and 24* in *peripheral enthesitis*, as assessed by WB-MRI, in patients with axSpA and PsA treated with ixekizumab.
3.	Change from baseline to *months 4 and 24* in *peripheral joint inflammation*, as assessed by WB-MRI, in patients with axSpA and PsA treated with ixekizumab.
4.	Change from baseline to *month 4* in *total inflammatory burden in the entire body* (peripheral and axial joints and entheses), as assessed by WB-MRI, in patients with axSpA and PsA treated with ixekizumab.
5.	*Description of differences between axSpA and PsA* inflammatory disease manifestations and their response to ixekizumab therapy at months 4, 12, and 24 (by sacroiliac joint and spine MRI and by WB-MRI).
6.	*Development of improved MRI and CT assessment methods* for axial structural damage assessment.
7.	Description of the *relationship between clinical, patient-reported, and imaging findings* at baseline and during ixekizumab therapy.

*WB-MRI* Whole body magnetic resonance imaging, *axSpA* axial spondyloarthritis, *PsA* Psoriatic arthritis, *CT* computed tomography

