### Statistics

#### Sample size calculation

The primary hypothesis of this study is that ixekizumab will reduce the total inflammatory burden in the entire body of patients with axSpA and PsA, as assessed by WB-MRI. All patients in this study will be treated with ixekizumab and the primary endpoint relates to identifying changes within groups. A guiding sample size calculation was done.

A previous investigator-initiated study with 53 axSpA patients treated with a bDMARD (golimumab) using WB-MRI as an outcome measure showed that the mean change in MRI-total inflammation (MRI axial inflammation + MRI peripheral inflammation (joints and entheses)) at week 52 was 24.8 (*p* < 0.001) with a standard error of 3.6 [55].

The change in WB-MRI total inflammation is the primary endpoint in the current study. If the expected mean of the paired differences is 24.8 and the expected standard deviation is 26.2 (corresponding to a standard error of 3.6) the study would require a sample size of 12 (numbers of pairs) to achieve a power of 0.80 and a level of significance of 0.05 (two-sided).

With an expected drop-out rate of 20% at month 12 the required sample size would be 14 patients.

It is planned to include 65 patients (≥25 with each diagnosis).

Sub-group analyses in regard to the primary endpoints for all groups (axSpA vs. PsA, WB-MRI remission vs. WB-MRI non-remission and clinical responders vs. clinical non-responders) are planned. For this matter, the calculated sample size is considered appropriate to detect a statistically significant change in the total inflammatory burden in the entire body as assessed by WB-MRI at month 12 in both the overall study population and in the individual sub-groups during treatment with ixekizumab.

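### The month-12 primary change is worded as the effect of ixekizumab, but patients above the activity cut-off at month 4 change treatment and stay in the analysis, so it estimates a start-with-ixekizumab strategy

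*Protocol article*

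**What the plan says.** All places are in the protocol article.

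- Introduction: "The primary objective is to assess the effect of ixekizumab on the total inflammatory burden in the entire body".
- Sample size calculation: the hypothesis is that "ixekizumab will reduce the total inflammatory burden in the entire body of patients with axSpA and PsA, as assessed by WB-MRI".
- Primary endpoint: "The primary endpoint is the change from baseline to month 12 in the total inflammatory burden in the entire body", in patients described as treated with ixekizumab.
- Assessments: there are eight clinic visits, "three of which are major assessment visits (months 4, 12, and 24"). At these, "Patients, who are not responding (defined as having ASDAS > 2.1 or DAPSA > 14), change treatment at the discretion of the treating rheumatologist" and under national guidelines. They are still followed in the study.
- Study interventions: ixekizumab dosing is described as running for the whole study, with no mention of the switch rule.
- Statistical analysis: the primary analysis is intention-to-treat in all included patients, with a per-protocol analysis for robustness. Within-patient change is tested by a paired t-test or Wilcoxon signed rank test.
- Study design: whole-body MRI is done at months 0, 4, 12 and 24.
- Table 3, key secondary endpoints: item 3 is the month-24 change in total burden. Item 5 describes structural change by conventional MRI, "MRI-based synthetic CT, low-dose CT, and radiography, during 2 years of therapy with ixekizumab".
- Table 3, other secondary endpoints, item 4 of 7: "Change from baseline to *month 4* in *total inflammatory burden in the entire body".

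**The concern.** The study has no control arm, so the within-patient change is all the evidence on the drug. A patient who switches after the month-4 visit contributes a month-12 scan taken after up to 8 months (12 − 4) on other treatment, and the endpoint wording counts that scan as change on ixekizumab. Switching is triggered by insufficient clinical response, so the scans affected are not a random sample. The Discussion argues that blinded image reading removes bias and makes a control group unnecessary. Blinding protects the reading of the scan, but it cannot tell the effect of ixekizumab from that of the treatment that replaced it.

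At stake is what the headline number may be said to show. The all-patient change at month 4, which precedes every protocol-directed switch, is placed a tier below the month-24 change, which follows two switch points (months 4 and 12).

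**Working it through.** **1. The plan's own figure.** The inputs, from Sample size calculation, are a mean change of 24.8 and a standard error of 3.6 in 53 patients. SD = 3.6 × √53 = 26.2, as stated. For a two-sided paired t-test at 0.05, 11 pairs give 80.7% power and 12 pairs give 84.7%, so the stated 12 pairs are adequate. The sample size is not in dispute.

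**2. Which scans precede a switch.** Set the scan schedule beside the treatment-decision visits:

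| Scan | Switch decisions already taken | Longest possible time on other treatment | Tier of total burden |
|---|---|---|---|
| Month 4 | none | 0 | other secondary, item 4 |
| Month 12 | month 4 | 12 − 4 = 8 months | primary |
| Month 24 | months 4 and 12 | 24 − 4 = 20 months | key secondary, item 3 |

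Month 4 is the only post-baseline scan before any protocol-directed switch.

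**3. What the month-12 mean contains.** Let p be the share who switch at month 4. Let g be the mean further fall in score at month 12 under the new treatment, compared with what the same patients would have had by staying on ixekizumab. Then

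all-patient mean fall = mean fall under ixekizumab alone + p × g.

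The documents give neither p nor g. The values below are assumptions that show the scale:

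| p | Switched, of 65 × 0.8 = 52 | g = −5 | g = 0 | g = 5 | g = 10 | g = 15 |
|---|---|---|---|---|---|---|
| 30% | 15.6 | −1.5 | 0 | 1.5 | 3.0 | 4.5 |
| 40% | 20.8 | −2.0 | 0 | 2.0 | 4.0 | 6.0 |
| 50% | 26.0 | −2.5 | 0 | 2.5 | 5.0 | 7.5 |

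Over g = 5 to 15 the shift is 1.5 to 7.5 points, or 1.5/24.8 = 6% to 7.5/24.8 = 30% of the planning value. The counts use the plan's 20% drop-out and assume that drop-out is unrelated to response.

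**4. Effect on the test.** Take the largest shift in the table away from the planning value: 24.8 − 7.5 = 17.3. With SD 26.2 and n = 52, the noncentrality is 17.3/26.2 × √52 = 4.8, and power stays above 99%.

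**5. Wording against the switch rule.** Key secondary endpoint 5 refers to two years of ixekizumab therapy, and Study interventions describes dosing for the whole study. Under Assessments, a patient may have had about 4 or 12 months of ixekizumab by month 24. These passages do not agree.

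**The case against.** The best defence is that intention-to-treat at month 12 is a legitimate choice, matches the week-52 planning data, and that patients treated with ixekizumab may simply name the enrolled cohort, all of whom start the drug. This stands as a reason to keep month 12 as primary. It does not cover the objective and hypothesis, which speak of the drug's own effect.

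A second defence is that the plan already handles switching. The responder strata use the same cut-offs as the switch rule, a per-protocol analysis is planned, the month-4 change is pre-specified, and a detailed SAP is promised. The strata do describe the groups, but they do not change what the all-patient figure means. A switch that the protocol directs need not be a protocol deviation, and removing switchers would leave patients selected for response. Analysis detail may be left to the SAP; endpoint wording and ranking are fixed in this article.

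Several stronger readings are tempting, and the documents do not support them:

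- *The primary result is inflated by 6–30%.* Both inputs are assumed. The phrase "change treatment at the discretion of the treating rheumatologist and according to the available guidelines" may cover whether to switch or only the choice of treatment, so the number switched is unknown. The further change g could be zero or negative. The Discussion itself notes that pain from enthesitis is hard to separate from central sensitization, so clinical non-response need not mean remaining MRI inflammation.
- *The primary test is undermined.* Step 4 shows otherwise at the planning values. One can construct a case where ixekizumab does nothing and only switchers improve, by 24.8 points, and the test still often succeeds. Nothing in the documents suggests that case.
- *Month 4 is ranked last.* It is item 4 of 7 in the lower tier, and no testing hierarchy or alpha allocation is stated. Its rank affects emphasis in reporting, not error control.

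**Conclusion.** The point holds as one of interpretation and endpoint wording. Followed exactly, the plan would credit change after a switch to ixekizumab, whereas the month-12 all-patient figure estimates a strategy of starting ixekizumab with switching allowed. The difference is p × g, with size and sign unknown; the 1.5 to 7.5 points are an illustration that rests on assumed switching of 30–50% and an assumed further fall of 5–15 points. It bears on the estimate and its attribution more than on power. The month-4 change is free of this component, but it does not make up for the missing control group. The change should be made, because it is cheap and alters what the trial can conclude. No view is taken on the clinical switch rule.

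**What to change.** 1. Keep month 12 as primary, and word the all-patient result as the effect of a strategy that starts with ixekizumab and allows switching. Align the objective and hypothesis with this.
2. Move the month-4 change in total inflammatory burden, in all patients, to the key secondary endpoints as the main on-drug companion.
3. Report how many patients switched, and the month-12 change by whether they were still on ixekizumab. Label this split as descriptive, because it is selected on response.
4. If the change to the last scan on ixekizumab is analysed, treat it as a sensitivity analysis and state that its scan time depends on response (month 4 for those who switch then, month 12 for the rest).
5. Reword key secondary endpoint 5 as change during 2 years of follow-up after starting ixekizumab.
6. Reconcile the description of treatment duration in Study interventions with the switch rule in Assessments.

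The cost is rewording, one change of rank and short additional reporting from scans already scheduled; no new visits or patients are needed. The SAP is still to be written before any analysis, so there is time. The downside is small: the on-drug estimate covers 4 months only and may be less favourable.

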#### Secondary endpoints

A description of key secondary and other secondary endpoints is provided in Table 3.

**Table 3 Tab3:** Description of endpoints

Primary endpoint	
1.	Change from baseline to month 12 in *the total inflammatory burden in the entire body* (peripheral and axial joints and entheses), as assessed by WB-MRI, in patients with axSpA and PsA treated with ixekizumab.
